## Abstract

**Background:**

Oppositional defiant disorder (ODD) is a major mental health concern and highly prevalent among children living in poverty-impacted communities. Despite that treatments for ODD are among the most effective, few children living in poverty receive these services due to substantial barriers to access, as well as difficulties in the uptake and sustained adoption of evidence-based practices (EBPs) in community settings. The purpose of this study is to examine implementation processes that impact uptake of an evidence-based practice for childhood ODD, and the impact of a Clinic Implementation Team (CIT)-driven structured adaptation to enhance its fit within the public mental health clinic setting.

**Methods/design:**

This study, a Hybrid Type II effectiveness-implementation research trial, blends clinical effectiveness and implementation research methods to examine the impact of the 4Rs and 2Ss Multiple Family Group (MFG) intervention, family level mediators of child outcomes, clinic/provider-level mediators of implementation, and the impact of CITs on uptake and long-term utilization of this model. All New York City public outpatient mental health clinics have been invited to participate. A sampling procedure that included randomization at the agency level and a sub-study to examine the impact of clinic choice upon outcomes yielded a distribution of clinics across three study conditions. Quantitative data measuring child outcomes, organizational factors and implementation fidelity will be collected from caregivers and providers at baseline, 8, and 16 weeks from baseline, and 6 months from treatment completion. The expected participation is 134 clinics, 268 providers, and 2688 caregiver/child dyads. We will use mediation analysis with a multi-level Structural Equation Modeling (SEM) (MSEM including family level variables, provider variables, and clinic variables), as well as mediation tests to examine study hypotheses.

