### Description of the conditions

The study consists of three arms: two active treatment and one comparison condition:The 4Rs and 2Ss Multiple Family Group interventionThe 4Rs and 2Ss MFG is a 16-week group for urban children of between 7 and 11 years of age with ODD and their caregiver(s). In this model, six to eight families meet in weekly sessions focused on addressing family and parenting factors associated with behavior problems [30–33]. Session content also addresses lack of social support and high stress, which are two factors known to hinder treatment attendance [34–36]. Families are provided with free childcare, transportation expenses, and a meal to address common logistical barriers to attendance [8]. Moreover, perceptual barriers, such as stigma and fears of being blamed for their child’s difficulties, are targeted through group processes which normalize family difficulties, validate their expertise in solving problems, and promote mutual aid [37]. Providers who participate in this condition will attend a 5-h training to learn the 4Rs and 2Ss MFG model; thereafter, they will participate in bimonthly supervision over the course of implementationThe 4Rs and 2Ss MFG + CITIn addition to implementing the model and receiving supervision, a CIT consisting of providers, a clinic director and supervisor will participate in ongoing meetings with the research team’s adaptation specialist for a guided analysis of the structure, content and processes of the treatment model, including those that are amenable to modification and those that must remain unchanged in order to maintain fidelityStandard careStandard care includes the services that the clinic normally provides to children with behavioral problems, including outpatient mental health therapy and pharmacology

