### Measures

Data collection will occur at baseline, 8, and 16 weeks from baseline, and at 6-month follow-up. Demographic characteristics about familial factors (e.g., age, race/ethnicity, family income) will be collected via a questionnaire used in prior studies. A separate demographic questionnaire will be administered to providers to gather information including their age, race/ethnicity, education, and credentials.

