**Fig. 2 Fig2:**
[figure not shown]
Analysis of mechanisms

We will employ mediation analysis with two-level MSEM models as explicated by Preacher, Zhang and Zyphur [57] and extended to three-level models by Preacher [57]. We will use a combination of limited information estimation frameworks (focused on sub-portions of the full model) and full information estimation frameworks (focused on the entire three-level model) to strategically answer questions. At level 1, child outcomes at the immediate post test are modeled as a function of the family predictors (see Fig. 2) using baseline measures of outcomes and family mediators as covariates, taking into account the clustering at the higher levels of the model. The follow-up (6-month) measures of the mediators and the outcomes are included within the model in a classic SEM panel model with autoregressive effects, thereby linking the follow-up data to the immediate post-test data. This is an advantage of using MSEM over traditional multi-level modeling. Different centering strategies (e.g., grand mean versus group mean) can be explored to garner various perspectives on the data. This feature of the model provides perspectives on aim 2 and the relative importance of paths g–l in Fig. 1. To ascertain perspectives of the effects of clinic-level variables on provider variables, random intercept MSEM with the provider-level variables can be estimated as a function of the clinic variables that include dummy coded treatment variables (4Rs and 2Ss MFG + CIT versus 4Rs and 2Ss MFG) impacting the clinic mediators of readiness, leadership support, and climate, which in turn, affect the provider-level intercepts. This modeling, or variants of it, address aims 3 and 4.

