### Trial status

Clinic recruitment for standard care has been completed. Data collection has been initiated, and one third (*n* = 792) of the sample of providers and caregivers have been enrolled. Clinic recruitment for MFG and MFG + CIT have been initiated, and some clinics have already completed training and have participated in adaptation meetings. Recruitment of clinics for the experimental arms will be ongoing until enrollment targets are met. Groups for both MFG and MFG + CIT are expected to begin in the first trimester of 2017. A populated Standard Protocol Items: Recommendations for Interventional Trials (SPIRIT) Checklist (see Additional file 1) and Figure ( see Fig. 3) for all study protocols are included as an additional file (see Additional file 1 and Fig. 3). A composition of the data monitoring commitee has also been included (see Additional file 2).

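### The last visit is timed from treatment completion, which standard care does not have, so its date in the comparator arm is undefined and may differ from the MFG arms

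*Protocol article*

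**What the plan says.** The abstract (Methods/design) gives the schedule as "baseline, 8, and 16 weeks from baseline, and 6 months from treatment completion". The Measures section repeats the first three times but states the last differently: "Data collection will occur at baseline, 8, and 16 weeks from baseline, and at 6-month follow-up". It does not say from what point the 6 months run.

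Under Description of the conditions, MFG is a 16-week programme in which "six to eight families meet in weekly sessions focused on addressing family and parenting factors". Standard care "includes the services that the clinic normally provides to children with behavioral problems", including outpatient therapy and pharmacology. No course length or end point is given for it.

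Under Analytic strategy (text following Fig. 2), "child outcomes at the immediate post test are modeled as a function of the family predictors", and then: "The follow-up (6-month) measures of the mediators and the outcomes are included within the model", as an autoregressive panel linked to the post-test data. A linear growth model over all four time points is offered as an alternative. Aim 1 concerns both short-term and longitudinal impact on child ODD and functioning, with standard care as the comparator, and these are the primary outcomes.

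**The concern.** A follow-up rule in a three-arm comparison has to give a date in every arm. This one gives a date only where treatment has a defined end. For standard care someone must either choose a substitute date or let each family's departure from care set it. The first leaves room for different choices at different clinics. The second makes the measurement time depend on behaviour after allocation.

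Either way, the 6-month wave may be observed at different times since baseline in different arms. Oppositional symptoms and impairment can change with time alone, so a difference in timing would be mixed with the treatment contrast at that wave. The panel model treats the wave as a single occasion. A growth model could use actual dates, but it would not remove a dependence of those dates on who leaves care and when.

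A secondary matter concerns week 16. Because that visit is counted from baseline, a group that starts well after a family's baseline would still be running when the post-test is taken.

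**Working it through.** **Inputs**

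- MFG length: 16 weeks (Description of the conditions).
- Last visit: 6 months after treatment completion (abstract), or 6 months with no anchor (Measures). Six months is taken as 26.1 weeks.
- Standard-care length or end: none given.
- Lag L from a family's baseline to its first group session: not given. Assumed range 0 to 16 weeks.

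The article states no follow-up time in weeks from baseline, so there is no figure of its own to reproduce first. The enrolment figures play no part in this point.

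**Last visit, MFG arms**

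Weeks from baseline = L + 16 + 26.1 = 42.1 + L.

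**Last visit, standard care: three readings**

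1. Week 16 plus 6 months: 16 + 26.1 = 42.1. The gap to MFG is (42.1 + L) − 42.1 = L.
2. Baseline plus 6 months: 26.1. The gap to MFG is (42.1 + L) − 26.1 = 16 + L.
3. Departure from care at week d, plus 6 months: d + 26.1. This varies by family and gives no date for a family still in care.

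Readings 1 and 2 differ by 42.1 − 26.1 = 16 weeks whatever L is.

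**Week-16 visit**

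Time since baseline is 16 weeks in every arm. Group weeks elapsed in MFG = max(0, 16 − L).

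| Assumed L (weeks) | Group weeks elapsed at week 16 | Share of 16 | MFG last visit (weeks from baseline) | Gap to standard care, reading 1 | Gap, reading 2 |
|---|---|---|---|---|---|
| 0 | 16 | 100% | 42.1 | 0 | 16 |
| 4 | 12 | 75% | 46.1 | 4 | 20 |
| 8 | 8 | 50% | 50.1 | 8 | 24 |
| 12 | 4 | 25% | 54.1 | 12 | 28 |
| 16 | 0 | 0% | 58.1 | 16 | 32 |

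**Is there a lag?**

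Three statements bear on it.

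- Families are consented consecutively (Participants) into groups of six to eight, so early families may wait for a group to fill.
- Clinic involvement reports data collection begun at 8 + 7 = 15 experimental-arm clinics.
- Trial status says that groups in those arms "are expected to begin in the first trimester of 2017".

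Together these make a lag plausible. None of them gives the interval for a family.

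**After the change**

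With the last visit timed from baseline at 16 weeks plus 6 months, it falls at 42.1 weeks in all three arms for any L. The sample size does not change.

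**The case against.** The strongest defence is that the article has a natural reading. Treatment lasts 16 weeks, the post-test is at week 16, and the 6-month wave is linked to the post-test in the panel model, so standard care would be followed at about week 42. On that reading the arms differ only by L, which may be zero. The article is also a condensation. Visit windows are commonly left to the full protocol, and the SPIRIT figure is not shown.

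The natural reading is sensible and may be what the investigators intend. But the article does not merely omit a detail. It states a rule that the comparator cannot follow, and elsewhere states the same visit without an anchor. The two statements need reconciling even if the intention is week 42.

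The defence does succeed against three stronger readings that a reader might infer.

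- **That the arms are measured at different times throughout.** The documents do not support this. The 8- and 16-week visits are counted from baseline in every arm. A late group start would mean incomplete exposure at week 16, not unequal timing.
- **That groups are known to start after families' baselines.** No interval is stated, and data collection covers providers as well as caregivers, so early data at experimental clinics could be provider data. The counts do lean the other way. If 37 clinics are enrolled and at least 15 are experimental, at most 22 are standard care. At 20 dyads and 2 providers each, those hold at most 22 × 22 = 484 of the 792 enrolled. That leaves 308 in experimental clinics, of whom 15 × 2 = 30 would be providers and about 278 caregivers. But this assumes that the two status statements share a date and that the planned numbers per clinic hold, and being enrolled is not the same as having completed baseline.
- **That the spread in follow-up times has a known size because many families leave early.** The Background's figure of nearly 50% premature attrition comes from the literature and carries no timing, and nothing in the article says that departure sets a family's visit date.

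**Conclusion.** The point holds for the last visit. Its anchor does not exist in standard care, and the two statements of the schedule do not agree on one. The standard-care date could be about week 42, about week 26, or set by departure, and the first two differ by 16 weeks with no further assumption than 6 months = 26.1 weeks. The difference between arms is L on the first reading and 16 + L on the second. Since L is not stated, the documents show that arm-dependent timing is possible, not that it has occurred or how large it is. It matters because this wave carries the longitudinal part of Aim 1 on the primary outcomes. It should be settled, and the correction is cheap.

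The week-16 point is secondary and conditional. If groups start well after a family's baseline, "child outcomes at the immediate post test" would be measured during MFG rather than after it, which would tend to dilute the effect. With assumed lags of 4 to 8 weeks, 12 to 8 of the 16 group weeks would have elapsed. Whether this happens cannot be determined from the article.

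**What to change.** Reconcile the abstract and the Measures section, and time the last visit from each family's baseline in all three arms at 16 weeks plus 6 months (about 42 weeks), whatever the attendance or completion. The same rule can be applied to standard-care families already enrolled, because their baseline dates are known. It is best settled before their last visits fall due.

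The cost is mainly a wording change to the schedule. The downside is that an MFG family whose group started late would be seen less than 6 months after the group ended, at 26.1 − L weeks (22.1 weeks if L = 4, 18.1 if L = 8). That loss is small if lags are short.

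For families not yet enrolled, taking baseline close to group start would limit both this shortfall and incomplete exposure at week 16. It costs some scheduling effort between consent and the first session. Restarting the clock for all visits from a group start date, with repeat baselines, is not needed: baseline is already an anchor that all three arms share.

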**Discussion:**

The aim of the study is to generate knowledge about effectiveness and mediating factors in the treatment of ODDs in children in the context of family functioning, and to propose an innovative approach to the adaptation and implementation of new treatment interventions within clinic settings. The proposed CIT adaptation and implementation model has the potential to enhance implementation and sustainability, and ultimately increase the extent to which effective interventions are available and can impact children and families in need of services for serious behavior problems.

**Trial registration:**

ClinicalTrials.gov, ID: NCT02715414. Registered on 3 March 2016.

**Electronic supplementary material:**

The online version of this article (doi:10.1186/s13063-017-2331-7) contains supplementary material, which is available to authorized users.

## Background

Oppositional defiant disorder (ODD) is a chronic and impairing mental health disorder that afflicts between 1 and 21% of the population, and primarily elementary school-age children, with the median age of onset being 11.6 years [1]. Along with conduct disorder and attention deficit hyperactivity disorder, ODD is part of the disruptive behavior disorder (DBD) diagnostic group, which is characterized by severe behavioral problems including impulsivity, aggression, violence, delinquency, and criminal acts [1].

Family poverty is one of the greatest risk factors for the onset and perpetuation of DBDs [2–4]: studies indicate that the accumulation of risk factors associated with poverty, including increased exposure to violence and traumatic events, devastating impact of substance abuse, criminal activity, and chronic disease, as well as family strain have an additive effect, in that the more risk factors a child is exposed to increases their likelihood of exhibiting serious behavioral challenges [1, 5]. Accordingly, children living in poverty experience DBDs at rates of up to four times higher than children reared in families with more financial resources [6].

Treatments for DBDs are among the most well-studied and efficacious [7], yet as many as 80% of children in poverty-impacted communities do not receive services. And for those who do manage to initially engage in behavioral health care, premature attrition from services approaches 50% [1, 8]. Further, the uptake of evidence-based practices (EBPs) in community-based settings is slow and beset with challenges. An oft-cited statistic suggests that it can take as long as two decades before treatments that are studied in research trials become integrated as part of standard practice in real-world settings [9] if at all. Thus, even though children who live in poor communities are at the highest risk for DBDs, they are the least likely to receive effective mental health services.

### The 4Rs and 2Ss Multiple Family Group (MFG) intervention

The 4Rs and 2Ss Multiple Family Group (4Rs 2Ss MFG) for Strengthening Families Program is an evidence-based, manualized, family based treatment for families of children with disruptive behaviors [10–15]. Recently listed on the Substance Abuse and Mental Health Services Administration (SAMHS) National Registry of Evidence-based Programs and Practices [16], this model is associated with high attendance rates, improvement in behavior problems, caregiver depression and stress among predominantly low-income, minority families [14].

### Conceptual model

The 4Rs and 2Ss MFG intervention draws from group therapy techniques, systemic family therapy, and behavioral parent training [12]. It was developed using a common elements approach [10], which entails identifying techniques and procedures that are common to already existing evidence-based protocols for specific problem areas [17]. As such, the 4Rs and 2Ss MFG integrates family processes and parenting skills linked to conduct problems from the empirical academic literature [10, 14]. The targeted skills and processes are referred to in the curriculum as the 4Rs (Rules, Responsibility, Relationships, and Respectful Communication) and 2Ss (Stress and Social support) [14]. Additionally, families of youth with DBDs and mental health providers assisted in the model’s development specific to enhancing cultural and contextual relevance of the intervention content, as well as engagement [10].

### Implementation processes

Although positive outcomes from the 4Rs and 2Ss MFG were found in prior studies, significant implementation challenges emerged [18]. Ongoing leadership support varied, and provider motivation waned in the presence of high levels of family engagement and intensity of family need. These findings suggested that the implementation of the 4Rs and 2Ss MFG required attention to multi-level implementation processes to modify service delivery practices on a sustainable level.

There has been a growing interest within the mental health field in implementation processes that facilitate the uptake and adoption of evidence-based practices in community-based settings [19, 20]. The adoption of EBPs is predicated upon both inner contextual factors pertaining to the organization, including the agency’s climate, leadership support, and provider perceptions about EBPs [21–26], and the larger external context in which the organization is embedded [23], including the political and legislative landscape that may mandate or enforce specific practices, and reimbursement mechanisms [21].

Hybrid effectiveness-implementation research designs were developed to focus both on an intervention’s effectiveness and implementation processes, either sequentially or simultaneously, which is proposed to accelerate the process to integrating EBPs in real-world practice settings [27]. As noted by Curran [27] there are three types of hybrid designs; examination of the intervention’s effects while observing implementation processes, examination of implementation processes while observing effectiveness, and examining both effectiveness and implementation simultaneously. This study will employ the latter, a Hybrid Type II design, which tests both clinical and implementation areas simultaneously [27].

### Purpose of this study

This study reflects a combination of clinical effectiveness and implementation research methods, with aims focused on replicating child outcomes associated with the 4Rs and 2Ss MFG, and gathering information about family and clinic/provider-level moderators of implementation. A secondary objective is to test an innovative method of adaptation of the 4Rs 2Ss MFG through the formation of change teams that are hypothesized to enhance outcomes and inner contextual factors. Within the academic literature on implementation processes, there is a growing emphasis upon staff serving as champions or change agents to implement EBPs and address potential barriers to adoption [25, 28, 29, 35]. In this study, providers and leadership will form a Clinic Implementation Team (CIT) and will be guided through a standardized process by which they adapt the intervention’s content, format, and structure. As shown in Fig. 1, a main premise of this study is that adaptation of 4Rs and 2Ss MFG by the CIT will impact clinic-level mediators of readiness, leadership support, and climate (path m) which, in turn, is proposed to affect provider-level variables (path n). These differential effects then carry through to the core family variables (path o) and, in turn, child outcomes (path p).

**Fig. 1 Fig1:**
[figure not shown]
Analysis of mediation

## Methods/design

### Study aims

In 2014, the National Institute of Mental Health (NIMH)-funded “Family Groups for Urban Youth with Disruptive Behavior.” The grant began with a planning stage in 2015 and will be completed by 2019. The four aims of the study are to examine:The short-term and longitudinal impact of the 4Rs and 2Ss MFG model on child ODD and functioningFamily level mediators, such as parenting and family processes, that impact child outcomesClinic- and provider-level factors (organizational culture and climate, leadership support, provider attitudes towards EBPs) upon implementation of the 4Rs and 2Ss MFG implementation, andThe impact of Clinic Implementation Teams on clinic- and provider-level moderators of 4Rs and 2Ss MFG implementation and integration

